#### Questionnaires

##### Anxiety disorder screening measures

Screening tools were selected based on two key criteria:*Evidence of accuracy:* Measures which have been found in prior research, of reasonable methodological quality, to demonstrate some evidence of diagnostic accuracy (i.e., minimally an AUC ≥ . 70, and a Youden’s index of ≥ 0.4), have been included.*Conceptually relevant:* Screening tools for which evidence of accuracy is not available but where the content is highly relevant have also been included.

To have the potential to be included based on screening accuracy, we required that the screening tool had been evaluated using sufficient quality methodology that the screening metrics could be deemed meaningful. Specifically, we required that the research assessed diagnostic accuracy in a perinatal population; employed some form of diagnostic assessment without knowledge of screening tool scores; assessed a minimum of three AD; and reported minimally AUC, and sensitivity and specificity for AD independently of other disorders. This represents a “softer” set of criteria than the full gold standard criteria, allowing us to determine which perinatal AD screening tools hold promise and should be further evaluated. Further, reported AUC values and *J*-Indices were required to meet or exceed 0.75, and 0.40, respectively.

Based on these criteria, we identified eight measures for inclusion in the current study: the STAI [92], the EPDS-3A [93], the GAD-7 [94], the K-10/K-6 [95], the MGMQ [5], the Perinatal Anxiety Screening Scale (PASS) [96], and the ANRQ-2A [97, 98]. Additional measures were assessed but performed too poorly to merit further evaluation: the KMMS [82] the EPDS [43], the GAD-2 [94], the Hospital Anxiety and Depression Scale – Anxiety (HADS-A) [99], the Pregnancy-Related Anxiety Questionnaire – Revised (PRAQ-R/R2) [100], and the Whooley [101]. Additional information about each measure is provided below.

State Trait Anxiety Inventory—Trait (STAI-T) [102]

The STAI-T is a 20-item self-report measure. Participants are asked to indicate how they feel in general on a 4-point Likert scale ranging from 0 (not at all) to 4 (very much so), in response to a variety of statement (e.g., “I have been nervous”). Scores less than 25 represent little to no anxiety, scores ranging from 26–40 represent moderate anxiety, scores over 40 represent high anxiety. The STAI-T has been used to assess clinical anxiety across many patient populations with a high Cronbach’s alpha of 0.90 [102]. The STAI has shown acceptable test–retest across samples (0.73-0.86) [102].

We elected to include the STAI-T was based on the single study of *N* = 100 pregnant people [79]. In this study, 5 of 8 AD were assessed, and both the AUC value (0.89) and the *J*-index (0.61) were above the threshold for a “good enough” screening tool.

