##### **Edinburgh Postnatal Depression Scale – 3 Anxiety Items (EPDS-3A)** [43]

The EPDS is a 10-item self-report measure screening tool, and is the most widely used screening tool for postpartum depression [43]. Items are rated from 0–3 and assess symptom severity over the last week, with 0 indicating no symptoms, and 3 indicating more severe symptoms of depression. All 10 items are scored to provide a sum score, with higher scores indicative of more severe depressive symptoms. The EPDS has been included in the current study for two reasons: (a) to screen for depressed mood, and (b) to be evaluated as a screening tool for perinatal AD.

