##### **Generalized Anxiety Disorder 7-item Scale (GAD-7)** [110]

The GAD-7 is a 7-item self-report measure designed to assess symptoms of generalized anxiety disorder (GAD) [110]. Items are rated on a Likert-type scale, ranging from 0 (not at all), to 3 (nearly every day). The GAD-7 has been found to demonstrate good reliability as well as convergent, criterion, construct, factorial and procedural validity [110, 111]. The GAD-7 is sensitive to change over time [111], and has been validated for use in the perinatal period [77]. Prior research has found a Cronbach's alpha of 0.92 for the GAD-7 [110]. The GAD-2 is a shortened version of the GAD-7 comprised of the first two items, with these items selected to capture the core diagnostic features of GAD [94].

Inclusion of this measure was based on two studies: one previously conducted by our team (*N* = 310) [46], and a second more recent publication (*N* = 954) [98]. In the first of these [46], we assessed the screening accuracy of the GAD-7 for all AD as a group, against DSM-IV criteria, among postpartum people. This resulted in an AUC of 0.78 and a *J*-index of 0.41, exceeding our threshold for inclusion. The second study’s [98] assessment of the screening accuracy of the GAD-7 was conducted in relation to five DSM-V AD (i.e., GAD, PD, AG, SAD and OCD) criteria. This resulted in an AUC of 0.82 and a *J*-Index of 0.51, also exceeding our threshold for inclusion. In the same study [98], the GAD-2 was also assessed for these disorders and resulted in even stronger screening metrics (i.e., an AUC of 0.83 and a *J*-Index of 0.52).

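### The GAD-2 is rejected for poor accuracy, although the article's own figures for it pass the stated inclusion rule

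*Protocol article*

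**What the plan says.** Under Anxiety disorder screening measures, the article sets out what prior evidence a tool needs to enter on accuracy grounds. The source study must be perinatal, must have made its diagnoses without knowledge of the screening scores, must have "assessed a minimum of three AD", and must report AUC, sensitivity and specificity for AD separately from other disorders. The numerical bar appears twice: first as "minimally an AUC ≥ . 70, and a Youden’s index of ≥ 0.4", then as AUC and J values that "were required to meet or exceed 0.75, and 0.40, respectively".

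The same section names the tools that entered on this basis and then a rejected group, introduced by "Additional measures were assessed but performed too poorly to merit further evaluation". The rejected list includes "the EPDS [43], the GAD-2 [94], the Hospital Anxiety and Depression Scale" and others.

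The GAD-7 section explains that "The GAD-2 is a shortened version of the GAD-7 comprised of the first two items". It justifies the GAD-7 by two studies, one of 310 postpartum people and one of 954 people. Of the second it adds that "the GAD-2 was also assessed for these disorders and resulted in even stronger screening metrics", with an AUC of 0.83 and a J of 0.52.

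The EPDS-3A section says that the EPDS is included for two reasons, to screen for depressed mood and "to be evaluated as a screening tool for perinatal AD". Table 1 lists the EPDS, without the 3A label, among the AD screening measures.

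**The concern.** The stated reason for leaving out the GAD-2 is poor performance, and the only performance figures given for it are good. The article accepts the same study as grounds for including the GAD-7.

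This bears on the core objective, which is to identify one or more accurate tools. The section on Research objectives says that recommendations will weigh accuracy together with feasibility, including length, administration time and scoring. A two-item tool with reported accuracy close to that of its seven-item parent is a natural candidate on those terms, yet the plan as written would not compare it with the others. If it were added after the data had been seen, the addition would look data-driven. The list of tools also fixes the family of pairwise tests to which the false-discovery-rate correction applies, so it should be settled before analysis.

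**Working it through.** **Inputs, all from the article.**

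- Inclusion bar (Anxiety disorder screening measures): AUC at least 0.70 in one sentence and 0.75 in another; J at least 0.40; at least three AD assessed.
- GAD-2, study of 954: AUC 0.83, J 0.52.
- GAD-7, same study: AUC 0.82, J 0.51. GAD-7, study of 310: AUC 0.78, J 0.41.
- Standard for a sufficiently accurate tool (Introduction): among its criteria, AUC at least 0.8 and J at least 0.5.

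**Step 1. The GAD-2 against the inclusion bar.**

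- AUC: 0.83 − 0.70 = 0.13 above the lower bar; 0.83 − 0.75 = 0.08 above the higher bar.
- J: 0.52 − 0.40 = 0.12 above the bar.
- Disorders: the GAD-7 section says that the study covered five AD for these tools. The EPDS-3A section describes the same study as covering four. Either exceeds three.
- Against the stricter standard in the Introduction: 0.83 ≥ 0.8 and 0.52 ≥ 0.5, so the AUC and J parts are met. Its other two parts (negative predictive value and positive likelihood ratio) cannot be checked, because the article does not give those figures for the GAD-2.

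**Step 2. Comparison with tools that were kept.**

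| Tool and evidence | AUC | J | Status |
|---|---|---|---|
| GAD-2, N = 954 | 0.83 | 0.52 | rejected |
| GAD-7, N = 954 | 0.82 | 0.51 | included |
| GAD-7, N = 310 | 0.78 | 0.41 | included |
| EPDS-3A, N = 310 | 0.76 | 0.42 | included |
| K10, N = 376 | 0.77 | 0.46 | included |
| K6, N = 376 | 0.77 | 0.45 | included |

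The reported values for the GAD-2 are higher than those of every included entry in this table.

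**Step 3. Is the GAD-2 better than the GAD-7?** The difference is 0.01 on each metric. The Hanley-McNeil standard error is SE² = [A(1 − A) + (n₁ − 1)(a − A²) + (n₀ − 1)(b − A²)] / (n₁n₀), with a = A/(2 − A) and b = 2A²/(1 + A). The test statistic is z = 0.01 / √(s₁² + s₂² − 2r·s₁·s₂). The article does not give the number of cases or the correlation r between the two AUCs, so both are assumed:

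| Assumed case share | Cases / non-cases | SE at 0.83 | SE at 0.82 | z at r = 0 | z at r = 0.9 |
|---|---|---|---|---|---|
| 5% | 48 / 906 | 0.0368 | 0.0376 | 0.19 | 0.60 |
| 10% | 95 / 859 | 0.0264 | 0.0270 | 0.26 | 0.84 |
| 20% | 191 / 763 | 0.0190 | 0.0194 | 0.37 | 1.16 |

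Across this range z runs from about 0.2 to 1.2. The advantage is numerical only.

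**Step 4. Size of the test family.** Count ten scores: STAI-T, EPDS-3A, GAD-7, K10, K6, MGMQ, PASS, ANRQ-2A, AD-22 and PASQ. AUC pairs now: 10 × 9 / 2 = 45. With the GAD-2: 11 × 10 / 2 = 55.

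**The case against.** The strongest defence is that other studies of the GAD-2 may have fallen short and that the authors judged the evidence as a whole. The cited sources are not at hand, so this cannot be ruled out. But the article reports no such result, and mixed evidence is not the rule it applies elsewhere: the EPDS-3A was kept although two studies missed the thresholds. Nor can the 954-person study be dismissed as too weak, since the article also relies on it for the EPDS-3A and the ANRQ-2A.

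A second objection is that the harm is small. This largely stands. The GAD-2 items are collected within the GAD-7, so no data are lost and no planned estimate for a listed tool is biased. What is lost is a pre-planned index test.

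Two stronger readings are tempting, and the article supports neither. A reader might infer that the GAD-2 has been shown to outperform the GAD-7; a gap of 0.01 in one study does not show that. A reader might also infer that the full EPDS is both rejected and included, and should be restored as an index test. The article separates the included EPDS-3A from the rejected EPDS total. The sentence on two purposes sits under the EPDS-3A heading. The depression subsection that follows uses the EPDS cut-off of 13, and the AD subsection turns to the three anxiety items. Table 1 can be read as naming the questionnaire administered. The article gives no AUC or J for the EPDS total against AD, so nothing in it shows that rejecting the total was wrong. What remains is loose wording.

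**Conclusion.** The point holds for the GAD-2. The article rejects it for poor performance, yet the only figures it reports clear the inclusion bar by 0.08 or 0.13 on AUC, depending on which version of the bar applies, and by 0.12 on J. Its accuracy in that study is about equal to that of the GAD-7. The conclusion rests on the article's account of one study, which the authors themselves accept as adequate evidence. It does not depend on the GAD-2 being superior. For the EPDS, only a clarification is warranted. The matter should be corrected before analysis, but it does not threaten the validity of the results for the tools already listed.

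**What to change.** Remove the GAD-2 from the rejected list, score it from the first two GAD-7 items, and name it as an index test in the ROC analyses and in the DeLong and McNemar comparisons. If evidence exists for leaving it out, state that evidence instead.

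In the same revision, give a single AUC threshold for inclusion, since 0.70 and 0.75 both appear. State in the EPDS-3A section and in Table 1 that the AD index test is the EPDS-3A or, if the ten-item total is also meant, say so. Close with one final list of index tests.

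No participant answers any extra question and no data collection changes. The cost is ten more AUC comparisons in the false-discovery-rate family (55 − 45, on the count of ten scores above), with corresponding additions for sensitivity and specificity.

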##### **Edinburgh Postnatal Depression Scale – 3 Anxiety Items (EPDS-3A)** [43]

The EPDS is a 10-item self-report measure screening tool, and is the most widely used screening tool for postpartum depression [43]. Items are rated from 0–3 and assess symptom severity over the last week, with 0 indicating no symptoms, and 3 indicating more severe symptoms of depression. All 10 items are scored to provide a sum score, with higher scores indicative of more severe depressive symptoms. The EPDS has been included in the current study for two reasons: (a) to screen for depressed mood, and (b) to be evaluated as a screening tool for perinatal AD.

##### Screening for depression

A cut-off score of 13 identifies pregnant and postpartum people with severe depressive symptoms that should be assessed further by healthcare practitioners for a depression diagnosis (42). A review paper of the EPDS reported sensitivity estimates ranging from 64 to 100% for identifying depression, and specificity range from 73 to 97% across included studies (*n* = 11) [103]. Although the EPDS has presented with variable levels of sensitivity and specificity in the literature, it is a widely used tool in English-studies [104], and has also been highly acceptable across different cultures [103]. The EPDS has acceptable reliability and internal consistency (Cronbach alphas from 0.82—0.84) [105], and is a common screening tool for depression during both pregnancy and the postpartum [103, 105].

##### Screening for perinatal AD

Three items have been frequently found to cluster on an anxiety factor leading to the creation of an anxiety subscale, the EPDS-3A, which can be used to screen for perinatal anxiety [93, 106]. Studies have found the optimal cut-off score for anxiety to be 4 or above [107], or 6 or above [108]. When a cut-off of 4 has been used, the EPDS-3A has resulted in a sensitivity of 63%, and specificity of 70% for detecting any anxiety disorder [107]. Importantly, it has been found that women who score high on the anxiety subscale tend to score relatively low on the total EPDS, indicating that their anxiety may have gone undetected had the EPDS-3A was not specifically used [108].

To our knowledge, a total of five studies have assessed the accuracy of the EPDS-3A as a screening tool for perinatal AD [5, 46, 77, 80, 109]. Of these, the measure demonstrated sufficient accuracy as to provide support for inclusion in the current research [5, 46, 98]. In two of these studies, the EPDS-3A was assessed among pregnant people [5, 98]. In the first of these three (5), the screening accuracy of the EPDS-3A was assessed for six AD among *N* = 214 pregnant participants. In the second study [98], four AD were assessed in a sample of *N* = 954 pregnant people at approximately 34-weeks’ gestation. The third study [46] to provide evidence of the screening accuracy of the EPDS-3A included assessments of all the AD, and involved *N* = 310 postpartum participants. All three studies employed DSM-IV diagnostic criteria. The two studies involving pregnant people resulted in AUCs of 0.82 and 0.81, and *J*-indices 0.42 and 0.54, respectively [5, 100]. The study involving postpartum people [46] resulted in an AUC of 0.76, and a *J*-index of 0.42. Neither of the remaining two studies to evaluate the EPDS-3A as a screening tool for perinatal AD [80, 109] resulted in screening metrics meeting required thresholds.

##### **Generalized Anxiety Disorder 7-item Scale (GAD-7)** [110]

The GAD-7 is a 7-item self-report measure designed to assess symptoms of generalized anxiety disorder (GAD) [110]. Items are rated on a Likert-type scale, ranging from 0 (not at all), to 3 (nearly every day). The GAD-7 has been found to demonstrate good reliability as well as convergent, criterion, construct, factorial and procedural validity [110, 111]. The GAD-7 is sensitive to change over time [111], and has been validated for use in the perinatal period [77]. Prior research has found a Cronbach's alpha of 0.92 for the GAD-7 [110]. The GAD-2 is a shortened version of the GAD-7 comprised of the first two items, with these items selected to capture the core diagnostic features of GAD [94].

Inclusion of this measure was based on two studies: one previously conducted by our team (*N* = 310) [46], and a second more recent publication (*N* = 954) [98]. In the first of these [46], we assessed the screening accuracy of the GAD-7 for all AD as a group, against DSM-IV criteria, among postpartum people. This resulted in an AUC of 0.78 and a *J*-index of 0.41, exceeding our threshold for inclusion. The second study’s [98] assessment of the screening accuracy of the GAD-7 was conducted in relation to five DSM-V AD (i.e., GAD, PD, AG, SAD and OCD) criteria. This resulted in an AUC of 0.82 and a *J*-Index of 0.51, also exceeding our threshold for inclusion. In the same study [98], the GAD-2 was also assessed for these disorders and resulted in even stronger screening metrics (i.e., an AUC of 0.83 and a *J*-Index of 0.52).

##### **Kessler Psychological Distress Scale (K6/K10)** [95]

The K10 is a self-report measure of psychological distress which can be administered as the full 10-item version (the K10) or the briefer, 6-item version (the K-6) [95]. The K6 is comprised of 6 items from the K10. Items are measured on a 5-point Likert scale ranging from 0 (none of the time), to 4, (all of the time). Total scores range from 0–24 for the K6, and 0–40 for the K10. Optimal cut-scores for the detection of DMS-IV mental health conditions have been suggested as 14 for the K6, and 24 for the K10 [112]. The K10/K6 has demonstrated consistently strong psychometric properties across a variety of sociodemographic samples [95], and the K6 has been found to have result in a sensitivity of 0.36 and a specificity of 0.96 in predicting serious mental illness in the general population [113].

The K10/K6 as a screening tool for perinatal AD has been evaluated in two studies [80, 81]. This resulted in two assessments of the K10 [80, 81], and one of the K6 [80]. The first assessment of the K10 as a screening tool for perinatal AD employed a representative sample of pregnant people (*N* = 129), and assessed 3 AD [81]. This evaluation resulted in AUC values of 0.71 and 0.76, and *J*-Indices of 0.48 and 0.75 (depending on the cut-score employed) [81]. The second study to evaluate the K10 as a screening tool for perinatal AD also employed a representative sample of pregnant people (*N* = 376), and included an assessment of all of the AD, resulting in an AUC of 0.77 and a *J*-Index of 0.46 [80]. This second study also included an assessment of the K6 which resulted in an AUC of 0.77 and a *J*-Index of 0.45.

##### **Matthey Generic Mood Question (MGMQ)** [5]

The MGMQ screens for a range of negative emotional states including depression and anxiety [5]. It consists of three questions pertaining to how the individual has been feeling over the past two weeks [5]. The first question (distress question) is related to feeling stressed, anxious, or unhappy (response options of ‘yes’, ‘possibly’ or ‘no’). If this initial question is endorsed, the individual is asked the two remaining questions: how bothered (bother question) they have been by these feelings (response options of ‘not at all’, ‘a little bit’, ‘moderately’, ‘a lot’), and what they think has caused their distress. Although the MGMQ appears to demonstrate a good–excellent level of accuracy in screening for perinatal anxiety disorders [114] publications related to this measure have not included metrics necessary to draw this conclusion with confidence [5], nor have they consistently differentiated screening accuracy for depression from screening accuracy for anxiety [85].

##### **Perinatal Anxiety Screening Scale (PASS) ** [96]

The PASS [96] is a 31-item self-report measure designed to screen for perinatal anxiety. Participants are asked to indicate how often they have experienced a variety of emotions/sensations (e.g., worry about the future) over the last two weeks. Items are scored via a 4-point Likert scale ranging from 0 (not at all), to 4 (almost always). Scores in the 0–20 range represent little to no anxiety, scores ranging from 21–41 represent mild-moderate anxiety, and scores ranging from 42–91 represent severe anxiety.

The inclusion of the PASS in the current study was based on a study in which the PASS, when administered to pregnant participants (*N* = 312), demonstrated very high accuracy against both DSM-IV and the ICD-10 diagnostic criteria (i.e., AUC values of 0.93 and 0.94, and *J*-indices of 0.76 and 0.79, respectively) [83]. However, the strong screening metrics obtained in this study may be attributable to the fact that study interviews were administered prior to questionnaire completion. Administration of the study interview prior to questionnaire completion may have resulted in participants providing responses more similar to those provided in the interview than would have been the case had the questionnaire been completed first.

##### **Antenatal Risk Questionnaire – 2 Anxiety Items (ANRQ-2A) ** [97]

The ANRQ is a 12-item questionnaire that assesses a range of content domains (e.g., emotional support from respondent’s own mother in childhood, history of mood disorder and treatment received, life stress) [97]. The ANRQ-2A is comprised of the two anxiety items from this measure, with higher scores indicating risk for perinatal mental health problems [95]. ANRQ scores have been shown to correlate with EPDS scores [115].

The ANRQ-2A was included based on a recent study of *N* = 954 people assessed in late pregnancy [98]. In this study, the accuracy of ANRQ-2A was assessed against DSM-IV diagnostic criteria. A cut-off of 6.0 on the ANRQ-2A resulted in an AUC of 0.84, and yielded a *J*-Index of 0.54 (in this case both sensitivity and specificity = 0.77), providing support for these items in routine screening [98].

##### **Anxiety Disorder—22 (AD-22) ** [116]

The AD-22 is a 22-item, self-report anxiety screening measure created for the current project [116]. Instructions, items, and scoring was adapted from a previous proof of principle screening accuracy assessment of 13 items (1–3 per disorder) taken from a variety of other self-report measure of specific anxiety conditions. The AD-22 measure includes items reflective of each of the core AD (i.e., PD, SAD, SP, GAD, AG, separation anxiety) as well as OCD and PTSD. Items were developed by our team of investigators. There are three items for each disorder with the exception of SP and AG for which there are two, respectively. Respondents are asked how bothered they have been by each of the 22 included symptoms/experiences of anxiety (e.g., difficulty controlling worry, feeling afraid of crowded spaces) over the previous two weeks. Items are rated on a Likert-type scale from 0 (not at all) to 4 (extremely).

This measure has been included in the current study as the 13-item version exceeded the required accuracy of a “good enough” screening tool [46]. Specifically, data from this study of N = 310 postpartum people resulted in an AUC of 0.86 and a *J*-index of 0.54.

